#### Second Round of the Delphi Survey: Selection of the Dose Recommendations From the Literature

After analysis of the first round, the experts will be asked to review the specific dose recommendations from the systematic literature search and select the recommendations they agree with. Additionally, they will be provided with (1) the authors’ justifications for their recommendations; (2) data from the LiverTox database; and (3) information from the corresponding SmPC on precautions, hepatotoxicity, and ADRs. If the experts completely reject the evidence, they will have the opportunity to enter their own alternative suggestions in a designated comment field. The second round is intended to allow for the analysis of differences between baseline routine clinical judgment and a subsequent evidence-informed reassessment in which experts can critically evaluate and either adopt or explicitly reject the published recommendations. Items for which first-round ratings diverge widely are of particular interest in this round as the provision of structured evidence may facilitate convergence. The design also enables meaningful analysis of substances where first-round consensus was already high to assess whether evidence confirms or challenges prevailing practice.

Of note, the provided data have the same content and structure as in the internal preassessment. For certain agents, the literature provides additional information, such as considerations for comorbidities, specific situations requiring further dose modifications, starting doses, maximum doses, or alternative agents appropriate in cirrhosis. Experts will be asked to provide a separate assessment on their agreement or disagreement for each Child-Pugh grade. The planned evaluation scales can be found in MultimediaAppendices 2  3, which provide the structured assessment forms applied in the second Delphi round. The final recommendation list will include dose recommendations for which consensus is reached.

### Application of Dose Recommendations in Patients

#### Objective of the Clinical Study and Study Design

Finally, the feasibility and acceptability of the adopted recommendations for drug selection and dosing in liver cirrhosis will be evaluated through a prospective, nonrandomized clinical study involving patients with liver cirrhosis with the following objectives: (1) improvement of drug therapy safety by applying the consensus-validated therapy recommendations in patients with liver cirrhosis and (2) demonstration of clinical usefulness of the consensus-validated therapy recommendations for patients with liver cirrhosis. For this purpose, dose recommendations will be provided to the pharmacists responsible for the wards with hepatologic patients. If discrepancies between the prescribed medication and the adopted dose recommendations are identified in a patient meeting the inclusion criteria, pharmacists will propose a dose adjustment; substitution with an alternative active substance; or another strategy mentioned in the dose recommendations, such as TDM or enhanced monitoring for adverse reactions. The acceptance of the recommendations remains at the discretion of the prescribing physician. The clinical study will be conducted in the hepatology department of University Hospital Bonn.

#### Inclusion and Exclusion Criteria

All adult (≥18 years) hospitalized patients with clinically documented liver cirrhosis of any origin and severity, except for pediatric patients, pregnant and breastfeeding women, and patients after liver transplantation, will be included. Furthermore, patients must be hospitalized for at least 24 hours and must be seen at least once by the pharmacist responsible for the ward.

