#### Primary and Secondary End Points

The primary end point of the study will be the comparison of the rate of deviations from the prescribed medications before and after the implementation of the consensus-validated dose recommendations. Specifically, the rate of deviations over 9 months using the recommendations (cohort B) will be compared with the rate of deviations over 9 months before their implementation (cohort A), first identified at the prescription level and subsequently aggregated at the patient level. A deviation will be defined as any prescription of a drug covered by the recommendations that does not match the corresponding recommendation for drug selection or dose adjustment, assessed at the patient level during the hospital stay. Prescriptions are assessed at the level of individual active substances. In patients with multiple relevant prescriptions, all prescriptions are checked individually for discrepancies. For the primary end point, deviations are assessed at the patient level as a binary outcome, defined as the presence of at least one deviation during the hospital stay (yes or no). Multiple deviations per patient are aggregated, with the primary outcome defined as the presence of at least one deviation per patient. The total number of MRPs per patient, including both clinically relevant (manifest or preventable) and non–clinically relevant MRPs, will be counted and subsequently dichotomized for categorical analyses. MRPs will be identified based on the first complete medication review at initial patient assessment. Combination products will be broken down into individual active substances if these are available separately; otherwise, they will be evaluated as a single entity. Physicians are given a predefined period of 3 days to address identified MRPs. Unresolved issues will be reassessed and counted thereafter. Recurring deviations after prior resolution will be counted as new events. Deviations from recommendations are treated as a process measure of prescribing behavior, whereas secondary end points are intended to characterize feasibility, acceptance, and safety-related process signals associated with implementation of the recommendations and, therefore, are interpreted as exploratory. These may include the acceptance and rejection rates of pharmacists’ recommendations, particularly for drugs with hepatotoxic properties; frequency of typical side effects (classified as “very frequent” or “frequent” according to the SmPC) of the prescribed drugs covered by the recommendations; deviations from recommended serum levels for drugs monitored via TDM; emergency readmission rates within 30 days after discharge; and overall hospital readmission rates. Furthermore, all consensus-validated recommendations rejected by the prescribing physician will be further analyzed with regard to the corresponding reasons.

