The primary objective is to assess whether implementation of the consensus-validated recommendations is associated with a lower rate of deviations from the recommendations regarding drug selection and dose adjustment. The primary comparison of deviations as defined in the Primary and Secondary End Points section between cohort A (before implementation) and cohort B (after implementation) will be performed using a chi-square test for the dichotomized end point; effect estimates will be reported as odds ratios with corresponding 95% CIs. Additionally, the raw number of deviations (counted as MRPs at the patient level) will be compared between the 2 cohorts using a nonparametric Wilcoxon rank-sum test. If substantial baseline differences between the cohorts are observed, adjusted analyses may be performed using regression models (eg, logistic regression for the binary outcome or Poisson or negative binomial regression for count data) including relevant baseline covariates to account for potential confounding. The main analysis will be conducted at the patient level. In a secondary analysis, the evaluation will be repeated at the prescription level; clustered data structures (multiple prescriptions per patient) will be accounted for using appropriate methods. As the primary objective is to compare prescribing behavior between 2 predefined cohorts within a real-world pretest-posttest design, the primary analysis will be conducted unadjusted for other covariates. To address potential bias, baseline characteristics will be described and compared between cohorts to assess potential imbalances. Furthermore, major organizational changes or parallel quality improvement initiatives related to medication safety will be documented and qualitatively considered when interpreting the results. An exploratory sensitivity analysis using logistic regression adjusting for key clinical variables (eg, age, sex, and Child-Pugh class) will be performed to assess robustness with regard to potential residual confounding. Secondary end points will be analyzed descriptively and, where appropriate, using inferential methods suited to the scale and distribution of the corresponding variables. If distributional assumptions for parametric testing are not met, appropriate nonparametric alternatives will be applied. Missing data will be handled via complete-case analysis without imputation; the extent and pattern of missingness will be described. No formal adjustment for multiple testing will be applied for secondary outcomes, and results will be interpreted accordingly. Analyses will be performed using R (version 4.4.2; R Foundation for Statistical Computing [19]) with RStudio (Posit PBC) [20]. Statistical significance will be set at a *P* value below .05.

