
As an additional unique feature of our approach, the second Delphi round represents a structured re-evaluation under enriched information conditions rather than a purely iterative consensus process. In this context, we plan to specifically provide information about the hepatotoxic effects of the drugs to the experts during the consensus process whenever such data are available [32]. Although Zimmerman [33] reported in 1978 that patients with cirrhosis do not experience drug-induced hepatotoxic effects more frequently than other patients, such events are associated with higher morbidity and mortality due to the preexisting vulnerability. Although only a few publications consider hepatotoxicity in their dose recommendations, we want to analyze whether this information from the literature and the SmPC affects expert decisions regarding dose adjustments. Our modified design of the 2-round consensus procedure allows for the analysis of how clinicians actually manage drug dosing in patients with cirrhosis in the absence of formal guidance and the comparison of how the provision of structured evidence influences expert decisions—a dimension not captured through the conventional approach.

One limitation of our study is the evaluation of a restricted number of drugs. However, we will focus on the drugs with the highest expected clinical relevance for the treatment of patients with liver cirrhosis, determined via reconciliation with the stock list of a hospital of maximum care covering all clinically common drugs and the assessment of relevance based on frequency of use, and on the need for dose adjustments in patients with cirrhosis, determined via an internal consensus procedure. In the future, this initial evaluation could be expanded to additional active substances following the same methodology. The weighting of assessment criteria and the predefined cutoff value for inclusion represent pragmatic thresholds defined to operationalize this prioritization strategy. These parameters are not based on statistical calculations and may limit external validity. As prescribing patterns, formularies, and patient populations may vary across institutions, the prioritization strategy applied in this study may reflect local clinical practice and, therefore, may require contextual adaptation when transferred to other health care settings.

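### Patients with no covered drug count as fixed non-events, and neither the primary chi-square test nor the raw-count comparison accounts for how many covered drugs a patient has

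*Protocol article*

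**What the plan says.** Inclusion and Exclusion Criteria takes adult "hospitalized patients with clinically documented liver cirrhosis of any origin and severity", with certain groups excluded. It adds that "patients must be hospitalized for at least 24 hours and must be seen at least once by the pharmacist responsible for the ward". Nothing there concerns what the patient is prescribed.

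Primary and Secondary End Points defines a deviation as "any prescription of a drug covered by the recommendations that does not match the corresponding recommendation for drug selection or dose adjustment". The outcome is then made binary per patient: "Multiple deviations per patient are aggregated, with the primary outcome defined as the presence of at least one deviation per patient".

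Statistical Analysis compares this binary outcome between cohorts with a chi-square test, without covariates. In addition, "the raw number of deviations (counted as MRPs at the patient level) will be compared between the 2 cohorts using a nonparametric Wilcoxon rank-sum test". The section also plans:

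- a secondary analysis at prescription level that allows for clustering;
- an exploratory logistic sensitivity model, with age, sex and Child-Pugh class as examples of covariates;
- regression models, including Poisson or negative binomial for counts, if the cohorts differ substantially at baseline.

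None of these names the number of covered drugs, and neither does the variable list in Data Collection and Security. The Discussion acknowledges the narrow list: "One limitation of our study is the evaluation of a restricted number of drugs".

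**The concern.** Taken together, the entry criteria and the deviation definition put two kinds of patient in one denominator: those who could have a deviation and those who could not. Among those who could, the chance of at least one deviation rises with the number of covered drugs, even when each prescription is handled equally well.

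Randomization would balance this exposure on average. Here cohort B follows cohort A in time and the primary test is unadjusted, so nothing balances it. If fewer cohort B patients need a covered drug, or they need fewer of them, the crude rate falls with no improvement in prescribing. If exposure rises, a real improvement is partly hidden. The primary odds ratio and the count comparison are both open to this.

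**Working it through.** **Inputs from the protocol article (Sample Size Calculation and Start of Study):** 35% versus 20%, two-sided 0.05, 80% power, 138 per group. **Assumed, because the document does not give them:** the share u of patients with no covered drug, and the number of covered drugs per patient.

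**1. The plan's own figure.** Chi-square formula with pooled variance and no continuity correction, mean proportion 0.275:

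n = [1.96 × √(2 × 0.275 × 0.725) + 0.8416 × √(0.35 × 0.65 + 0.20 × 0.80)]² / 0.15² = (1.2377 + 0.5239)² / 0.0225 = 137.9, so 138 per group. Power at 138 is 80.0%. The stated figure reproduces.

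**2. Shift in the unexposed share, prescribing quality unchanged.** Let 35% be the all-patient rate in cohort A. The rate among exposed patients is 0.35 / (1 − u_A), and cohort B's crude rate is that value times (1 − u_B).

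| u_A | u_B | Rate if exposed | Crude rate in B | Odds ratio | Chance the test favours B |
|---|---|---|---|---|---|
| 10% | 20% | 38.9% | 31.1% | 0.84 | about 10% |
| 10% | 30% | 38.9% | 27.2% | 0.70 | about 29% |

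The last column is the probability of a significant result in B's favour with 138 per group; the nominal value in that direction is 2.5%. For the first row: (0.0389 × √138 − 1.96 × √(2 × 0.3306 × 0.6694)) / √(0.2275 + 0.2143) = (0.457 − 1.304) / 0.665 = −1.27, and Φ(−1.27) ≈ 0.10. The spurious differences are 3.9 and 7.8 points, about a quarter and a half of the 15-point target.

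**3. Shift in the number of covered drugs, per-drug risk q unchanged.** With k covered drugs and independent deviations, P(any) = 1 − (1 − q)^k.

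- 3 drugs to 2: q = 1 − 0.65^(1/3) = 0.134, and 35% becomes 25.0% (test favours B about 44% of the time).
- 4 drugs to 3: q = 0.102, and 35% becomes 27.6% (about 26%).
- If the number of covered drugs is Poisson, a 20% lower mean in B gives 1 − 0.65^0.8 = 29.2% (about 18%), whatever the starting mean.

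The first two lines take a whole drug from every patient and are upper illustrations.

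**4. Does the unexposed share cost power?** That depends on the denominator of the 35%, which is not stated.

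- If 35% and 20% are all-patient rates, the non-events are already in them and 138 per group keeps its 80%.
- If they apply only to patients with a covered drug, both are multiplied by (1 − u): power falls to 74.1%, 67.4% or 60.0% for u = 10%, 20% or 30%.

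**The case against.** The strongest objection is to the remedy that first suggests itself. A reader might infer that the primary population should be cut to patients with a covered drug, or the primary model adjusted for their number. The documents do not support that. The recommendations include avoidance, substitution and drug selection, so whether a patient receives a listed drug is partly what the intervention aims to change. Measuring exposure before the pharmacist's proposal removes the effect of that patient's own proposal. It does not remove learning on the ward over cohort B's nine months. An all-patient primary denominator is defensible, and this part of the objection stands.

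Three further points stand in whole or in part:

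- **Size.** Every exposure share above is an assumption. Frequency of prescription in cirrhosis is one criterion for putting a drug on the list, and the stock-list filter removes drugs that are not regularly used, so the unexposed share may be small. The cohorts are consecutive, in one department with stable staff, which makes large shifts less likely but does not exclude them.
- **Existing analyses.** The prescription-level analysis has covered prescriptions as its unit and answers part of the concern. It is secondary and does not correct the patient-level odds ratio or the Wilcoxon comparison.
- **Length of stay.** A reader might infer that longer stays mechanically produce more deviations. The end-point section bases identification of medication-related problems on the first complete medication review, so the text does not clearly support this. It also refers to the whole hospital stay, but that is a separate ambiguity.

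The article's statement that the design does not permit causal inference limits how the result may be read. It does not show whether exposure changed between periods.

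**Conclusion.** The concern holds in a limited form. The protocol article's own text makes patients without a covered drug fixed non-events, and the primary test and the raw-count comparison carry no term for exposure. With no change in prescribing quality, a 10-point shift in the unexposed share (10% to 20%) moves 35% to 31.1% and gives about a 10% chance of a result favouring cohort B. A 20-point shift (10% to 30%) moves it to 27.2% and gives about 29%. These figures assume 35% as the all-patient rate in cohort A, 138 per group and an equal deviation rate among exposed patients in both periods. They show what could happen; the document does not show that such a shift occurs.

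A reader might infer that the trial is underpowered through dilution. That does not follow: the sample size is correct for its stated inputs, and power is lost only if the 35% excludes patients without a covered drug, which the article does not say. Nor is the choice of an all-patient primary analysis wrong in itself. What is missing is a way to tell a change in exposure from a change in prescribing.

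**What to change.** Keep the all-patient chi-square test as the primary analysis, and fix the following before the cohorts are compared:

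1. Report by cohort the share of patients with at least one covered drug, and the number of covered drugs per patient, at the first complete medication review.
2. Add a prespecified sensitivity analysis of the primary outcome in patients with at least one covered drug at that review.
3. Add the number of covered drugs at that review to the logistic sensitivity model already planned.
4. Replace the Wilcoxon test on raw counts, or accompany it, with a negative binomial model with the number of covered prescriptions as offset, or a clustered binomial model with that number as denominator.

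The cost is a little more analysis work and one derived variable. Prescriptions are already to be checked one by one, so the count should be obtainable, and the article describes the analysis as still to come. The drawback is that results conditioned on exposure can miss benefit gained by avoiding listed drugs altogether. They should be read beside the all-patient result and not replace it.

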#### Primary and Secondary End Points

The primary end point of the study will be the comparison of the rate of deviations from the prescribed medications before and after the implementation of the consensus-validated dose recommendations. Specifically, the rate of deviations over 9 months using the recommendations (cohort B) will be compared with the rate of deviations over 9 months before their implementation (cohort A), first identified at the prescription level and subsequently aggregated at the patient level. A deviation will be defined as any prescription of a drug covered by the recommendations that does not match the corresponding recommendation for drug selection or dose adjustment, assessed at the patient level during the hospital stay. Prescriptions are assessed at the level of individual active substances. In patients with multiple relevant prescriptions, all prescriptions are checked individually for discrepancies. For the primary end point, deviations are assessed at the patient level as a binary outcome, defined as the presence of at least one deviation during the hospital stay (yes or no). Multiple deviations per patient are aggregated, with the primary outcome defined as the presence of at least one deviation per patient. The total number of MRPs per patient, including both clinically relevant (manifest or preventable) and non–clinically relevant MRPs, will be counted and subsequently dichotomized for categorical analyses. MRPs will be identified based on the first complete medication review at initial patient assessment. Combination products will be broken down into individual active substances if these are available separately; otherwise, they will be evaluated as a single entity. Physicians are given a predefined period of 3 days to address identified MRPs. Unresolved issues will be reassessed and counted thereafter. Recurring deviations after prior resolution will be counted as new events. Deviations from recommendations are treated as a process measure of prescribing behavior, whereas secondary end points are intended to characterize feasibility, acceptance, and safety-related process signals associated with implementation of the recommendations and, therefore, are interpreted as exploratory. These may include the acceptance and rejection rates of pharmacists’ recommendations, particularly for drugs with hepatotoxic properties; frequency of typical side effects (classified as “very frequent” or “frequent” according to the SmPC) of the prescribed drugs covered by the recommendations; deviations from recommended serum levels for drugs monitored via TDM; emergency readmission rates within 30 days after discharge; and overall hospital readmission rates. Furthermore, all consensus-validated recommendations rejected by the prescribing physician will be further analyzed with regard to the corresponding reasons.

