For feasibility reasons, and to focus on active substances particularly relevant in cirrhosis, a preselection will be conducted through an internal preassessment procedure to rate (1) the relevance of dose adjustments of each active substance considering the severity of potential ADRs mentioned in the literature, (2) the frequency of prescription particularly in patients with cirrhosis, and (3) the expected benefit of dose adjustment to avoid possible side effects. The expert panel will consist of 2 hepatologists and 1 clinical pharmacologist. Each expert will have specific expertise in the treatment of patients with liver cirrhosis. The following data from the selected literature will be the basis for the evaluation: (1) the authors’ recommendations and their justification; (2) further information from the references on hepatotoxicity and ADRs; (3) information from the corresponding SmPC on precautions, hepatotoxicity, and ADRs; and (4) information from the LiverTox database, assigned to category A, B, C, D, or E* in the Categorization of the Likelihood of Drug-Induced Liver Injury. For analysis of the assessments, the 3 different criteria (clinical relevance of ADRs, frequency of use, and expected benefit of dose adjustment) will be weighted in a ratio of 3:1:2. Considering the point scale from 0 to 3 provided to the experts, a maximum of 18 points per active substance can be achieved. Only the most relevant active substances rated, reaching a predetermined minimum score of 13.5 points, will be included for further processing. The cutoff is pragmatically predefined to focus on substances with the highest expected clinical impact and to improve the feasibility of the consensus evaluation.

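### The exploratory side-effect end point follows only drugs on the recommendation list, so substitution in cohort B can make that cohort look safer without any change in harm

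*Protocol article*

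**What the plan says.** The first objective of the clinical study is "improvement of drug therapy safety by applying the consensus-validated therapy recommendations in patients with liver cirrhosis" (Objective of the Clinical Study and Study Design). The primary end point is a process measure, deviation from the recommendations. The side-effect item among the secondary end points is the listed outcome closest to drug harm.

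That item carries two restrictions (Primary and Secondary End Points). The effect must be labelled frequent or very frequent in the SmPC, and it must be a side effect "of the prescribed drugs covered by the recommendations". No denominator is given, and nothing says that reactions to a drug outside the list are counted when it replaces a listed one.

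Where a prescription departs from a recommendation, the ward pharmacist may propose a dose adjustment, "substitution with an alternative active substance", or another strategy such as drug monitoring or closer observation. The prescribing physician decides whether to accept.

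The same end-point section presents the secondary end points as possibilities and as exploratory. The Statistical Analysis section has them analysed descriptively, with inferential methods where appropriate.

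**The concern.** The end point is tied to a set of drugs, and the intervention can move patients out of that set. Before implementation, a patient on a listed drug who is not switched stays under observation for this outcome. After implementation, a patient switched to an unlisted drug leaves observation at the switch, and whatever the replacement does is not recorded here. Ascertainment then differs between cohorts because of the intervention itself. A lower side-effect frequency in cohort B could be read as support for the safety objective when it partly reflects reactions that nobody counted.

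**Working it through.** **The plan's own figures.** The article states no figure for the side-effect end point. Its only sample-size figure, for the primary end point, reproduces. With 35% against 20%, two-sided 0.05 and 80% power, the pooled chi-square formula gives n = [1.960·√(2·0.275·0.725) + 0.842·√(0.35·0.65 + 0.20·0.80)]² / 0.15² = 137.9, so 138 per group. This point does not change it.

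**Can a replacement be unlisted?** In the internal preassessment the three criteria (ADR relevance a, frequency of use f, benefit of adjustment b, each 0 to 3) "will be weighted in a ratio of 3:1:2", and a drug goes forward only on "reaching a predetermined minimum score of 13.5 points". So 3a + f + 2b ≥ 13.5.
- With f and b at maximum, 3 + 6 = 9, so a ≥ (13.5 − 9)/3 = 1.5.
- With a and f at maximum, 9 + 3 = 12, so b ≥ (13.5 − 12)/2 = 0.75.

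A substance rated below either value cannot be on the list. This shows that a replacement can be unlisted. It does not show how often, since the article gives neither the final list nor the replacements.

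**Size for a per-patient rate.** Let e be the share of patients on a listed drug, s the extra share in cohort B moved to an unlisted drug, q the side-effect risk on the listed drug, r the risk on the replacement, and t the fraction of q that arises before the switch.
- Counted in A: e·q.
- Counted in B: (e − s)·q + s·t·q.
- If r = q, the true risk ratio is 1 and the counted ratio is [e − s(1 − t)]/e. At t = 0 this is (e − s)/e, the lowest possible value; as t approaches 1 it approaches 1.

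None of e, s, q or t is in the article. Assumed ranges: e = 50–100%, s = 5–15 points, q = 10–30%. Results at t = 0:

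| e | s | counted risk ratio |
|---|---|---|
| 50% | 5 / 10 / 15 points | 0.90 / 0.80 / 0.70 |
| 80% | 5 / 10 / 15 points | 0.94 / 0.88 / 0.81 |
| 100% | 5 / 10 / 15 points | 0.95 / 0.90 / 0.85 |

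The spurious absolute drop is s·q, from 0.05 × 0.10 = 0.5 to 0.15 × 0.30 = 4.5 percentage points. In the extreme corner (15% against 10.5%, 138 per cohort) a chi-square test would be significant with probability about 0.20. The main risk is therefore a misleading estimate more than a false significant result.

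The upper value of s matches the planned fall in the deviation rate, 35% − 20% = 15 points. That fall covers every type of correction, so 15 points would require all of them to be switches to unlisted drugs.

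**Size for a rate per covered prescription.** If q is the same on all listed prescriptions, the expected rate is q in both cohorts and the mechanical drop disappears. The replacement's reactions are then in neither numerator nor denominator, and the prescriptions left in cohort B are a selected set.

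**The case against.** Several points on the other side stand.
- The end point is exploratory and only a possible item on the list, and the Discussion disclaims causal inference. The primary analysis is untouched.
- The mechanical drop depends on a denominator that the article does not give and may leave to a fuller document.
- Deviations are found at the first medication review, when the listed drug is already prescribed, and physicians then have 3 days to act. Reactions before the switch count.
- Dose adjustment, drug monitoring and closer observation keep the patient in the count, and acceptance is discretionary.
- If the replacement is truly safer (r < q), part of the drop is real. At t = 0 only the uncounted s·r is artefact.

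These points limit size and certainty. They do not remove the problem, because under either denominator the replacement's reactions are missing.

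A reader might go further and infer that cohort B must look safer by construction, that the apparent reduction equals the share of prescriptions substituted, or that replacements are usually unlisted. The article supports none of these. The first depends on the denominator, the second is an upper bound under a per-patient rate, and the third needs a list that is not shown.

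A reader might also infer a bias from the SmPC-frequency filter, since drugs are listed partly on ADR severity while the end point counts by frequency. The filter applies equally to both cohorts, so it creates no difference between them. It is a scope limit: severe but uncommon reactions are not captured by this end point. Readmissions and the severity grading of medication-related problems reflect them only indirectly.

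**Conclusion.** The point holds in a limited form. As written, the side-effect end point follows listed drugs only, and the intervention can move cohort B patients to unlisted ones, so the comparison can favour cohort B with no change in harm. The size cannot be determined from the article. For a per-patient rate with equal true risk, the counted risk ratio is no lower than 0.70 to 0.95 across the assumed ranges of e and s, and nearer 1 once reactions before the switch are allowed for. For a rate per covered prescription there is no mechanical drop, but the omission remains. This is a moderate matter of end-point definition, worth settling before analysis because the outcome bears on the stated safety objective and exploratory status does not correct a directional error.

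**What to change.** In both cohorts, count side effects per patient for every listed drug prescribed during the stay and for any drug that replaces it. State the denominator. Keep the covered-drug count as now written beside it, so that the effect of the extension is visible. Report patients with a substitution separately from those with a dose change. Add a sentence acknowledging that uncommon severe reactions lie outside this end point because of the SmPC-frequency filter; the filter itself need not change for the cohort comparison.

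The cost is a change of wording and some additional chart review, limited to patients with a substitution. The data come from the routine clinical information system, but the clinical phase began in January 2025 and results are expected in late August 2026, so for patients already discharged the review would be retrospective. The cohort B rate may look less favourable than under the present definition.
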